Having successfully completed the pilot study, we present the protocol for the next study stage, which plans to conduct a prospective randomized controlled trial using the study tool among healthy older people. Specifically, the study objectives are to investigate the effectiveness of a remotely delivered personalized 8-week multicomponent exercise program based upon remote individual fitness assessment, compared either to the updated WHO guidelines (active-control) or to no intervention (control). We hypothesize that participants in the personalized experimental group will show greatest motor improvement in balance, strength, and flexibility than participants with similar baseline fitness profiles in the active-control, with least changes observed among the control group.

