## Measurements

### Remote fitness assessment tool

We will use standard movement performance tests selected by experts and incorporated into the smartphone application (EncephaLog™) developed by Montfort Brain Monitor LTD, utilizing the standard smartphone sensors - accelerometers and gyroscopes. The assessment will include 10 performance tests, operationalized to generate a total of 42 digital markers (see Table 1 and Additional file 1). Briefly, the 10 performance tests assess the following fitness components: static balance, dynamic balance, leg strength, upper body flexibility, and upper extremities strength. Raw data will be uploaded to the remote pooled databank. An example showing graphical demonstration of the raw data collection for the “one-leg stance” is presented in Fig. 4.

**Table 1 Tab1:** Outcome measures

Fitness Components	Tests	Digital Markers	Good performance
Static balance	^a^One-leg stance 10 s.	For each test: average acceleration (m/sec^2^) and angular velocity (radians/sec), in different directions.	*Lower scores – lower sway*
	^a^Tandem stance 20 s.		
Dynamic balance	Tandem walk: 10 steps forwards		
	Tandem walk: 10 steps backwards		
Legs strength	Sit-to-stand 10 rep.	Total time (sec.) and average duration for each rep.	*Shorter duration*
Upper body flexibility	^a^Torso rotation	Angle	*Increased angle - a greater range of motion*
	^a^Arm flexion		
	^a^Arm extension		
Upper extremities strength	^ab^Lifting arm forward 20 rep.	Average duration (sec.)	*Shorter duration*
	^ab^Lifting arm to side 20 rep.		

^a^For left and right separately

^b^with 0.5 kg for women and 1 kg for men

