### Sample size and power analysis

Statistical power was calculated using G * Power [26]. Based on the analysis, 100 participants in each of the 3 treatment groups (experimental, active control, control) enable detecting group differences in statistical power of 86% for a small effect size (Cohen’s f = .15), and in statistical power of 99% for a moderate and high effect sizes (Cohen’s f = .25, .40 respectively). In addition, the statistical power for detecting differences between repeated measures, and in the interaction between groups in the repeated measures is higher than 99% in the moderate effect size as well as in the high effect size.

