#### Data analysis

The following 2-ways ANOVAs with repeated measures (3 treatment groups X 4 times measurements – T1-T4) will be conducted for each digital marker as follows:For all participantsSeparately for each of the following four subgroups: young women and young men (age 65-74), and old women and old men (age 75+).Separately for each of the two levels of fitness (Low and High) for each component. For example: low level of balance performance in the experimental group (personalized) compared to low level of balance in the control groups.Bonferroni will be used for post-hoc analyses, and False Discovery Rate [27] will be used to account for multiple comparisons.

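### Bonferroni for the post-hoc comparisons is valid but needlessly conservative; Holm gives the same familywise error control and never rejects less

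*Protocol article*

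**What the plan says.** The Data analysis section of the Protocol article plans a two-way repeated-measures ANOVA ("3 treatment groups X 4 times measurements – T1-T4) will be conducted for each digital marker"). It then sets the multiplicity rule in one sentence: "Bonferroni will be used for post-hoc analyses, and False Discovery Rate [27] will be used to account for multiple comparisons". It does not say which comparisons make up the post-hoc family, what significance level applies, or how the two adjustments combine.

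The Remote fitness assessment tool section describes "10 performance tests, operationalized to generate a total of 42 digital markers". The Background states the objective as the personalized program "compared either to the updated WHO guidelines (active-control) or to no intervention (control"). Its hypothesis reads: "participants in the personalized experimental group will show greatest motor improvement in balance, strength, and flexibility than participants with similar baseline fitness profiles". The comparison meant there is with the WHO-guideline arm, and the untreated arm is expected to change least.

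The Sample size section plans "100 participants in each of the 3 treatment groups (experimental, active control, control"). Its power figures are for overall group, time and interaction effects. None is for a single pair of arms after the post-hoc adjustment.

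**The concern.** An overall test across three arms cannot show that the personalized program beats the WHO-guideline arm. The pairwise comparisons have to do that, and they are the ones given the Bonferroni adjustment. If the family is the three arm pairs, each pair is tested at 5%/3 = 1.67%, whatever the other two show.

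Holm's procedure starts at the same threshold and relaxes it after each rejection, with the same familywise error rate and no added assumptions. With exactly three arms one can go further. If one pairwise null hypothesis is false, at most one of the other two can be true, so after the first rejection both can be tested at the full 5%. This is Shaffer's step-down.

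What is at stake is power for experimental versus active control. The hypothesis places the active-control arm between the other two, so this difference is expected to be smaller than the one between experimental and control, and it is the one most exposed to a strict threshold.

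**Working it through.** **Inputs.** From the Protocol article: three arms, 100 per arm, 42 markers, four measurements. Assumed because the article does not state them: two-sided 5% level; a family of three arm pairs on one quantity for one marker; no dropout; no False Discovery Rate gate in front of the pairs; and the arm means below, in units of the residual SD.

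**1. The plan's own power figures.** The article gives "statistical power of 86% for a small effect size (Cohen’s f = .15") and "statistical power of 99% for a moderate and high effect sizes (Cohen’s f = .25, .40 respectively"). For the between-group effect in a repeated-measures ANOVA the noncentrality is λ = f² × N × m / (1 + (m − 1)ρ), with N = 300, m = 4, 2 and 297 df, and ρ = 0.5 assumed:
- f = 0.15: λ = 0.0225 × 300 × 4 / 2.5 = 10.8, power 84.2% (ρ = 0.46 gives 86%)
- f = 0.25: λ = 0.0625 × 1200 / 2.5 = 30, power 99.9%
- f = 0.40: λ = 0.16 × 1200 / 2.5 = 76.8, power above 99.9%

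The stated figures reproduce, but they describe the overall group test and not a pair of arms.

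**2. Rules compared, with the three p-values ordered p(1) ≤ p(2) ≤ p(3).**
- Bonferroni: every p against 5%/3
- Holm: p(1) against 5%/3, then p(2) against 5%/2, then p(3) against 5%, stopping at the first failure
- Shaffer (three arms only): p(1) against 5%/3; if rejected, the other two against 5%, in order

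Each threshold in a lower line is at least as generous as the one above it, so Holm rejects whatever Bonferroni rejects, and Shaffer whatever Holm rejects.

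**3. Power for experimental versus active control.** 400,000 simulated data sets per setting, pooled variance with 297 df:

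| Means (exp./active/control, SD) | Bonferroni | Holm | Shaffer |
|---|---|---|---|
| 0.5 / 0.25 / 0 | 26% | 34% | 41% |
| 0.6 / 0.3 / 0 | 39% | 50% | 56% |
| 0.4 / 0 / 0 | 66% | 70% | 74% |

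Hand check of the Bonferroni column: the pairwise t has noncentrality d / √(2/100) and critical value 2.408. For d = 0.25, 0.30 and 0.40 the noncentrality is 1.77, 2.12 and 2.83, and the power 26%, 39% and 66%.

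**4. Error rates.**
- All three arms equal: within-marker familywise error is 4.4% for each of the three rules, because they share the first step.
- Experimental and active control equal, both different from control (0.5/0.5/0): the false-positive rate for that pair is 1.7% (Bonferroni), 4.0% (Holm) and 5.0% (Shaffer).

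**5. Where the gain shrinks.**
- Family spanning visits: with 9 contrasts (3 pairs × 3 changes from T1, ρ = 0.5), power for the T3 change in one assumed scenario is 52% with Bonferroni and 57% with Holm. With only the three pairs at T3 it is 67% and 75%.
- Power already high: at f = 0.25 on the average of four measurements with only the experimental arm different, it is 99.0%, 99.4% and 99.6% for Bonferroni, Holm and Shaffer.

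**The case against.** Bonferroni is a standard and valid adjustment, and a condensed article may leave the detail to an analysis plan that is not shown. It is fair to say that nothing here is an error, and a reader who infers that the planned tests are invalid would be wrong. But the article does name the method, and the alternative needs no extra data, gate or choice of visit. The suggestion is therefore more than taste.

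A second objection is that the stricter rule protects against false claims of superiority over WHO advice. This stands in part. If the two exercise arms are equal and both differ from control on every marker, the expected number of false positives for that pair over 42 markers is 42 × 1.7% ≈ 0.7 with Bonferroni, 42 × 4% ≈ 1.7 with Holm and 42 × 5% = 2.1 with Shaffer. These rates stay within the nominal 5% per marker, but the change is not free.

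A reader might also infer that Bonferroni is dominated by a closed test that opens with the overall 2-df F test at 5% and then tests each pair at 5%. That does not hold strictly. With 297 df Bonferroni rejects at |t| > 2.408. If the third mean lies midway, F = t²/2, so the F gate (3.026) opens only at |t| > √(2 × 3.026) = 2.460. Bonferroni rejected a pair that the gated test missed in about 0.1–0.3% of simulated data sets. If the gate were the F test after the False Discovery Rate step, power would be lower still and would depend on a threshold that the article does not fix. Holm and Shaffer avoid this.

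Finally, the three-pair family and the 5% level are assumptions. Holm's advantage does not depend on either; Shaffer's 5%/3-then-5% rule does need the three-pair family.

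**Conclusion.** The point holds as a matter of efficiency. For any family of comparisons and any level, Holm controls the same familywise error rate as Bonferroni and never rejects less. Where the family is exactly the three arm pairs on one quantity for one marker, Shaffer's step-down is also valid and stronger.

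In the three settings examined, power for experimental versus active control rises by 4 to 11 points with Holm and by 8 to 17 points with Shaffer (differences of the unrounded figures: 3.2 to 10.8 and 7.6 to 16.9). These gains rest on the assumed means, a two-sided 5% level, three pairs, 100 per arm, no dropout and no False Discovery Rate gate. They compare the rules and do not forecast the power of the trial's complete procedure.

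The documents do not support reading this as lost error control, nor as a change without any cost: the false-positive rate under a partial null moves up towards 5%, and Bonferroni's simple simultaneous confidence intervals, which the article does not mention, are given up.

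**What to change.** In the Data analysis section, replace Bonferroni with Holm for the post-hoc comparisons, and state which comparisons form the family and at what level. If the family is defined as the three arm pairs on one quantity for one marker, Shaffer's step-down may be named instead: smallest p-value at 5%/3 and, once that is rejected, the other two at 5%. If the family also spans visits, stay with Holm.

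The False Discovery Rate step across markers is unchanged. The cost is one or two sentences, written before the unblinded data are analysed, with no extra participants or measurements. If simultaneous intervals for the arm differences are wanted, report Bonferroni intervals alongside and note that they may not match the step-down decisions in every case.

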## Discussion

This approach provides new potential solutions to combat the decline in physical activity which accompanies advancing age [28], and which has recently witnessed further exacerbation due to social isolation caused by the COVID-19 pandemic [29]. Furthermore, this model takes into consideration the increasing variability in fitness parameters, which like numerous other biological markers, exhibit a widening inter-individual variability with advancing age [4].

The current study serves to strengthen the proof of concept which underlies our study tool, combining both personalized exercise programs and individualized fitness assessment together with smartphone technology. The innovative technology will create a validated digital app which is dedicated to providing assessment of motor fitness along with a dynamic exercise program individually tailored based on the older person’s current ability level. If the study is successful, the results will serve to deepen contemporary approach to personalized exercise programs among the rapidly growing older population, and may serve as the baseline for numerous variations of personalized exercise programs. Furthermore, programs can be streamlined to incorporate variations based on the person’s movement preferences, and targeted at specific populations such as people confined to wheelchairs, those with mild cognitive limitations, as well as pre-frail or even frail individuals. Given the global pandemic of physical inactivity, and based on trend towards ever more personalized medicine, this innovative concept of a personalized exercise program may be further developed for use in all ages and at all functioning levels.

## Limitations

In order to avoid small comparison groups which may create statistical difficulties, we will apply only two levels of difficulty for each of the three movement components (eight lessons). As data from testing accumulates, we will apply three or more levels of difficulty for each component across different groups, enabling providing more accurate individualized exercise programs.Although the photos (videos) of the exercises, which have been produced by a professional photographer, are very clear, and presented on a stabilized (on a stand) mobile phone, the display of the mobile phone is nonetheless rather small. Our plan is to find a simple technological solution for transferring the videoed exercise programs to big screens (e.g. Television screen).There is a built-in conflict between the concept of personalized exercise tailored according to one’s needs, and performed at home at any convenient time, and the social benefits attributed to group exercise. To overcome this limitation, our future plan is to create, in addition to individual exercise programs, group activity programs where each person is performing his/her personal program.Conceptually, personal preferences should be considered in individually tailored exercise program. Due to methodological limitations (keeping the study well-controlled), we will not incorporate the person’s movement preferences into the objective levels of fitness in this study.

## Data Availability

The datasets generated during and/or analyzed during the study will be available from the corresponding author on reasonable request.

## Abbreviations

WHO: World Health Organization
AI: Artificial intelligence
T0-T4: Time 0 – time 4
Mini-Cog test: Mini cognition test
Acc: Accelerometer
Gyro: Gyroscope
ML: Medio-lateral
AP: Anterior-posterior
SI: Superior-inferior
POMS: Profiles of Mood States
PI: Principal investigator
ANOVA: Analysis of variance
HTTPS: Hypertext Transfer Protocol Secure
SSL: Secure Sockets Layer
